**DRUG SUPPLIES AND FINANCIAL SUPPORT**

Pfizer Inc. Clinical R & D (Gastroenterology / Hepatology) Global Research and Development Sandwich, Kent. United Kingdom

List of Abbreviations

The following abbreviations and special terms are used in this study protocol.

| Abbreviation or special term | Explanation |
| --- | --- |
| AE | Adverse event |
| AUC | Area under the curve |
| BP | Blood pressure |
| BID | Two times daily |
| CRF | Case report form |
| ECG | Electrocardiogram |
| EEG | Electroencephalography |
| Ethics Committee | Synonymous to Institutional Review Board and Independent Ethics Committee |
| GCP | Good Clinical Practice |
| CGRP | Calcitonin-gene related peptide |
| ICH | International Conference on Harmonisation |
| IRB | Institutional Review Board |
| NGF | Nerve growth factor |
| mBPI-sf | Modified brief pain inventory-short form |
| OAE | Other Significant Adverse Event |
| QOLQ | Quality of life Questionnaire |
| PDQ | Pain DETECT questionnaire |
| PGIC | Patient Global Impression of Change |
| PDT | Pain detection threshold |
| PK | Pharmako kinetic |
| Principal investigator | A person responsible for the conduct of a clinical study at a study site. Every study centre has a principal investigator. |
| SAE | Serious adverse event |
| SD | Standard deviation |
| SUSAR | Suspected Unexpected Serious Adverse Reaction |
| SP | Substance P |
| VAS | Visual analogue scale |
| WHO | World Health Organisation |

**SCHEDULE OF ACTIVITIES**

| **Protocol Activity** | Screen  **Day**  **-28 to -7** | Day 1 | Day 4 | Day 7 | Day 11 | Day 14 | Day 17 | End of Treatment and follow up  **Day 21 + 14 j** | Day 21 + 14 and 7 days forward |
| --- | --- | --- | --- | --- | --- | --- | --- | --- | --- |
| Informed Consent | X |  |  |  |  |  |  |  |  |
| Specific Medical History and Physical Examination | X |  |  |  |  |  |  |  |  |
| General Medical History and Physical Examination | X |  |  |  |  |  |  |  |  |
| Weight | X |  |  |  |  |  |  | X |  |
| Laboratory |  |  |  |  |  |  |  |  |  |
| Haematology | X |  |  |  |  |  |  | X |  |
| Blood Chemistry | X |  |  |  |  |  |  | X |  |
| Urinalysis | X |  |  |  |  |  |  | X |  |
| Coagulation | X |  |  |  |  |  |  | X |  |
| Pregnancy test a | X |  |  |  |  |  |  | X |  |
| ECG | X |  |  |  |  |  |  | X |  |
| Registration/Randomization | X |  |  |  |  |  |  |  |  |
| Study Treatment |  |  |  |  |  |  |  |  |  |
| Dosing pregabalin c |  | X --------------------------------------------------------------------------------- X | | | | | | | |
| Assessments |  |  |  |  |  |  |  |  |  |
| Skin | X | X |  |  |  |  |  | X |  |
| Muscle | X | X |  |  |  |  |  | X |  |
| Cold pressor test | Xd | X |  |  |  |  |  | X |  |
| Concomitant Medication e | X |  |  |  |  |  |  | X |  |
| Questionnaires |  |  |  |  |  |  |  |  |  |
| QOLQ f | X |  |  |  |  |  |  | X |  |
| mBPI-sf g | X |  |  |  |  |  |  | X |  |
| PD-Q h | X |  |  | X |  |  |  | X |  |
| PGIC i | X |  |  | X |  |  | X | X |  |
| Patient pain diary | X | X | X | X | X | X | X | X |  |
| Interview |  |  | X | X | X | X | X | X |  |

a Pregnancy tests will be done in females not postmenopausal for more than 1 year or sterilised.

c 75mg BID Day 1-3, 150mg BID day 4 – 7, 300mg BID Day 8 – 21 + 14 days followed by a 1 week medication taper, on half their maximum tolerated dose

d Cold pressor test training

e Concomitant medications will be assessed and noted at screening. Randomized patients will be advised to maintain their usual medication. As needs pain medication will be recorded in the diary.

f Quality of life Questionnaire

g Modified brief pain inventory-short form

h Pain DETECT questionnaire

i Patient Global Impression of Change. The PGIC questionnaire will be administered during outpatient clinic visits on Days 1 and Day 21+ 14 days and by telephone on days 7, and 17.

## Indication

Chronic Pancreatitis

## Background and Rationale

### Chronic Pancreatitis

The aetiology of pain in chronic pancreatitis remains to be elucidated. Therefore no common guidelines for the management of the pain exist and it is a topic of great discussion. The area is further complicated by the fact that only a few clinical trials have been carried out (Wilder-Smith *et al.* 1999 [1]). The best attempt to establish clear guidelines for the treatment of chronic pancreatitis is “American Gastroenterological Association Medical Position Statement: Treatment of Pain in Chronic Pancreatitis” (Warshaw *et al.* 1998 [2]). Initial treatment consists of low fat diet and non-narcotic analgesics, which can be supplemented by oral pancreatic enzymes and proton pump inhibitors. If an acceptable level of pain relief is not obtained with these drugs, only opioids remain for the management of pain. Opioids have a number of well-known adverse effects including elevation of smooth muscle tone (affecting gastrointestinal motility), toxicity in the central nervous system and especially induction of addiction. Many patients suffering from chronic pancreatitis have a history of alcoholic abuse making opioids, with their associated abuse potential, less suitable for these patients. Alternatives to medical treatment exist in the form of nerve blockade, lithotripsy and surgical treatment. However, results from studies of non-medical treatment modalities are equivocal and medical analgesic therapy must still be considered as the first choice in the management of painful chronic pancreatitis. Thus the importance of identifying potential new treatment regimes for the treatment of pain in chronic pancreatitis is clear.

### Clinical versus Experimental pain

Basic mechanisms in pain perception, transduction and processing can be explored by means of human experimental pain models. These models, when applied to healthy volunteers or to patients, provide an important translational link between preclinical animal testing and human clinical trials. In clear contrast to clinical pain, experimental pain models allow the possibility of controlling the duration, the intensity and the nature of the pain stimulus. Thanks to the exact control of the stimuli, the effects of analgesics can be assessed by performing standardized tests before and after analgesic administration. As pain is a multidimensional perception it is obvious that the reaction to a single stimulus of a certain modality only represents a limited part of the pain experience and therefore a variety of stimulus modalities and methods for pain assessment are required. Analgesics may differ in their effectiveness, influenced by both the nature of the stimulus and the tissue under investigation. This explains the importance of testing different tissues with multimodal pain models. By these methods, the most comprehensive and differentiated information about the analgesic of interest is obtained.

In the present study we have chosen to stimulate the skin and muscle in patients with chronic pancreatitis to elucidate changes in central pain transduction and processing. It has been shown previously that patients with chronic pancreatitis have hypoalgesia to visceral stimulation and this was found to be true for both the duodenum and the oesophagus. Further, an increased size of the referred pain area was found for the patients compared to healthy controls (Dimcevski *et al*. 2006 [3]; Drewes *et al*. 2006 [4]). The hypoalgesia to direct stimulation may reflect increased activity in descending control systems capable of dampening the peripheral input, whereas the increase in the somatic referred pain area to the same visceral stimulations probably reflects central hyperexcitability. Well established and validated models for multimodal stimulation of rectum exist (Drewes *et al*. 2002 [5] & 2003a [7]).

Recently an experimental pain model has been used to compare the effect of oxycodone (thought to work at the κ-opioid receptor in the peripheral visceral afferents) and morphine in equipotent doses (Staahl *et al.* 2006 [6]). The model compared the effect of the opioids on multimodal pain stimulations in the skin, muscle and esophagus. The study showed that oxycodone attenuated visceral pain better than morphine (and placebo) and hence elucidated a new aspect of visceral pain treatment that could never have been found in conventional phase 3 studies. In another recent study we showed that gabapentin was effective in attenuating deep muscle pain, a finding that is consistent with the wide use of this drug in various complex pain syndromes (Arendt-Nielsen *et al*. 2007 [8]).

### Treatment of neuropathic pain with pregabalin

Central sensitization is an essential factor in the development of neuropathic pain (Baron 2001 [9], Johnson *et al.* 2001 [10]) and in animal experiments the NMDA receptor has been shown to be involved in this process. Calcium plays a central role, as an increased influx of calcium into the neuron is observed when the NMDA receptor is activated. The enhanced concentration of intracellular calcium functions as a second messenger for a number of neurotransmitters and calcium thus contributes to the maintenance of the central sensitization (Nicholson 2000 [11]).

Pregabalin exerts a range of effects in pain transmission and although the precise mechanism of action is not completely understood, it likely involves the binding of the drug to calcium channels in the central nervous system (Ben-Menachem 2004 [12]). In animal experiments it has been shown that pregabalin primarily exerts its effect in the dorsal horn, where a reduced pain signal is seen. Pregabalin is a ligand of the α2-δ subunit of the voltage-gated calcium channel and binding of pregabalin to this site results in reduced calcium influx at the nerve terminals and therefore a reduced release of several excitatory neurotransmitters, including glutamate, substance P (SP), calcitonin-gene related peptide (CGRP) and noradrenaline. This may result in inhibition or reduction of the sensitization mentioned above. Moreover, this may be the basis for the analgesic effect. It has been shown, in animal experiments, that binding of pregabalin to calcium channels is able to counteract central sensitization in the dorsal horn.

The evidence for the clinical effect of pregabalin in neuropathic pain is substantial and is documented in a number of randomized clinical trials (Dworkin *et al.* 2003 [13], Sabatowski *et al.* 2004 [14], Rosenstock *et al.* 2004 [15]). The recommended dose for treating neuropatic pain is between 150 mg to 600 mg daily, which is similar to the dose chosen for this study.

### Neuropathic pain and chronic pancreatitis

In patients with chronic pancreatitis the pancreatic nerves have been found to have a greater diameter and the area innervated by a single nerve is smaller (Bockman *et al.* 1988 [16]). A neural genesis of pain therefore seems likely. The basis of the neurogenic generation of pain may be due to an altered expression of neuropeptides like SP and CGRP. The concentration of nerve growth factor (NGF) and its receptor TrkA is increased in inflammatory areas which may lead to an enhanced transcription of SP and CGRP, both of which are transmitters in the pain system (Di Sebatiano *et al.* 2003 [17]). Interestingly, the release of SP is known to be reduced by agents such as pregabalin.

Support for a neuropathic component of the pain of chronic pancreatitis is also found in clinical observations, where the pain is typically described as largely constant background pain with shooting, burning and lancinating episodes that may mimic that seen in peripheral neuropathies. Finally, evidence for central neuroplastic findings and strong descending inhibition, which may reflect the pain mechanisms in neuropathic pain have been found in recent studies (Dimcevski *et al.* 2006 and 2007 [18, 19]). Thus neuropathic and “true” visceral pain components appear to play a role in pancreatic pain. Hence the potential to extrapolate from clinical trials demonstrating the activity of pregabalin in the treatment of neuropathic pain to the treatment of the possible neuropathic component of chronic pancreatitis is of great interest.

# STUDY OBJECTIVES AND ENDPOINTS

The aim of the study is to investigate the effect of pregabalin in pain resulting from chronic pancreatitis. The effect will be investigated by means of questionnaires concerning the daily experience of pain and the general quality of life. Furthermore the patients will be invited to participate in a programme of human experimental pain testing (quantitative sensory testing = QST). The results from human experimental pain testing may help us to understand the mechanisms of action of pregabalin in this patient population.

## Objectives

The present study consists of two parts: one clinical and one involving human experimental pain testing (i.e. QST). In the clinical part the aim is to investigate the effect of pregabalin on clinical pain resulting from chronic pancreatitis. In the clinical part of the study, the primary objective is to understand the effect of pregabalin on the daily pain experienced by patients with chronic pancreatitis.

The experimental part aims at evaluating the effect of pregabalin using QST in controlled and standardized circumstances. In the experimental part of the study the primary objective is to understand the effect of pregabalin on altered pain processing in patients with chronic pancreatitis.

In the clinical part of the study a secondary objective is to understand the effect of pregabalin on the quality of life of patients with chronic pancreatitis. Further secondary objectives are to understand the safety and tolerability of pregabalin in this patient population.

## Endpoints

### Primary Endpoints

The primary endpoint for the study is analgesic effect of pregabalin therapy.

In the *clinical part* of the study, the primary efficacy parameter for analgesic effect is pain relief. This is defined as the reduction in VAS pain scores at the end of the study (day 21) as compared to the pre-treatment level. This effect is further assessed as changes in the daily experience of pain, which will be assessed using questionnaires, including the modified brief pain inventory-short form (mBPI-sf), the pain*DETECT* questionnaire (PD-Q, Freynhagen *et al*. 2006 [21]) and patient global impression of change (PGIC, Farrar *et al*. 2001 [22]).

In the *experimental part*, the primary endpoint for analgesic effect is change in pain processing. This is defined as the reduction pain tolerance thresholds in the dermatomes at the end of the study (day 21) as compared to the pre-treatment level. Pain processing will be assessed using QST parameters. All changes are compared to baseline recordings.

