### Secondary Endpoints

Secondary efficacy parameters are changes in quality of life compared to baseline level. The European Organization for research and treatment of cancer quality of life questionnaire (QOLQ, Bloechle *et al.* 1995 [23], will be used. Also the tolerability of the drug in this patient population will be compared to placebo.

In the experimental part of the study the difference of the QST stimulus are considered secondary efficacy parameters. The experimental baseline recordings will also be compared to published normal values from healthy controls to evaluate general aspects of pain processing in the patient group.

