## Skin and muscle stimulation

### Tetanic electrical skin stimulation

Thresholds to electrical constant current skin stimulation (Digistim; Biometer A/S, Copenhagen, Denmark; tetanic stimulation at 100Hz, 0.2ms square waves, self-adhesive electrodes 3cm apart) will be measured at the following left-sided sites: thorax (T4 dermatome), pancreatic site (dorsal T10 dermatome), arm (C5 dermatome), hip (L1 dermatome) and knee (L4 dermatome). Three thresholds will be measured: sensation (stimulation just felt, VAS = 1), pain detection (PDT, pricking pain just felt, VAS = 5) and pain tolerance threshold (PTT, burning pain, VAS = 7). These quantitative sensory testing (QST) techniques in relation to pancreatitis have been described in detail previously (Buscher *et al*., 2006 [28]).

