### Deep muscle stimulation

The pressure pain tolerance threshold (PPTT) will be determined on the quadriceps muscle and on the same localizations as the tetanic electrical skin stimulation by pressing an electronic pressure algometer (Somedic AB, Stockholm, Sweden) on the muscle group. The probe has a surface area of 1cm2. The pressure will be increased at a rate of 30 kPa/sec until the PTT (VAS = 7) is reached.

The patients will be instructed to press a button when PTT is reached.

PPTT is determined to be the average of 2-3 consecutive assessments separated by two-minute intervals.

The assessment parameter will be mean value of PPTT in kPa.

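### The experimental primary endpoint takes a reduction in pain tolerance thresholds as analgesia, but by the protocol's own definition of the threshold analgesia is an increase

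*Protocol*

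**What the plan says.** Protocol section 2.2.1 (Primary Endpoints) opens the experimental part neutrally: "the primary endpoint for analgesic effect is change in pain processing". The next sentence gives a direction: "This is defined as the reduction pain tolerance thresholds in the dermatomes at the end of the study (day 21". Pre-treatment level is the comparator. The section adds that pain processing is assessed with QST parameters, and names no site, modality or composite.

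Section 7.2.1 (Tetanic electrical skin stimulation) defines the electrical measure as "pain tolerance threshold (PTT, burning pain, VAS = 7", under constant-current stimulation. The sites are "thorax (T4 dermatome), pancreatic site (dorsal T10 dermatome), arm (C5 dermatome), hip (L1 dermatome) and knee (L4 dermatome".

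Section 7.2.2 (Deep muscle stimulation) describes the pressure measure: "The pressure will be increased at a rate of 30 kPa/sec until the PTT (VAS = 7) is reached". It is called PPTT, is recorded in kPa, and is taken on the quadriceps and "on the same localizations as the tetanic electrical skin stimulation".

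Section 2.2.2 (Secondary Endpoints) states: "In the experimental part of the study the difference of the QST stimulus are considered secondary efficacy parameters".

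In section 9, primary endpoints go to ANCOVA and changes in secondary endpoints to the Mann-Whitney U test. Both are presented with 95% confidence intervals. Alpha is 0.05 in the sample-size section, with no statement of whether tests are one- or two-sided.

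**The concern.** The sentence that defines success for one of the trial's two parts points the wrong way. Read literally, a drug that makes patients reach VAS = 7 at less current or pressure shows analgesic effect, and a drug that lets them tolerate more does not. The protocol is the dated record of what was to count as a positive result. If the direction is put right only when results are known, the correction looks like a choice made after seeing the data.

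Two looser points sit in the same definition. It speaks of thresholds in several dermatomes without saying which one, or what combination, carries the primary conclusion. The wording in section 2.2.2 could also be read to place the same thresholds among the secondary endpoints, where a different test applies.

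**Working it through.** **No plan figure to reproduce.** Section 9.1.2 sizes the experimental part on a decrease in pain VAS, not on any threshold, so it gives no number for this endpoint. The check is mainly a comparison of passages.

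**Direction.**
1. Both threshold definitions (7.2.1, 7.2.2) fix the response at VAS = 7 and record the stimulus needed to reach it.
2. Let T be that stimulus. Less pain at a given stimulus means a larger T is needed to reach VAS = 7. Analgesia is T(end) − T(baseline) > 0, and larger on pregabalin than on placebo.
3. Section 2.2.1 defines the effect as a reduction, R = T(baseline) − T(end), with R > 0 as benefit. That is the negative of the quantity in step 2.
4. In the clinical paragraph of the same section the outcome is a VAS score. There a reduction is the correct direction. The same word does not carry over to a threshold.

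**Effect on the analysis.** Let Δ be the adjusted treatment difference in T. Coding the outcome as R gives −Δ with the same standard error. The confidence interval (L, U) becomes (−U, −L), |t| is unchanged, and so is the two-sided p-value. Only a one-sided test, or a written success rule, taken in the literal direction would give a different decision. The protocol states neither.

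**Number of thresholds.**
- Electrical tolerance thresholds: T4, T10, C5, L1, L4 = 5.
- Pressure tolerance thresholds: the same 5, or 6 with the quadriceps.
- Total: 5 if the word dermatomes means the electrical skin sites; 5 + 5 = 10 or 5 + 6 = 11 if pressure is included.

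Five is the more natural count. Section 7.2.1 attaches the word dermatome to the electrical sites, and section 7.2.2 gives the muscle measure its own abbreviation.

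**Conditional error rate.** Suppose each of k thresholds were tested at 0.05 and any single one could carry the claim. Under independence the family-wise error is 1 − 0.95^k:

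| k | Calculation | Family-wise error |
| --- | --- | --- |
| 5 | 1 − 0.95^5 | 22.6% |
| 10 | 1 − 0.95^10 | 40.1% |
| 11 | 1 − 0.95^11 | 43.1% |

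Thresholds within a patient are correlated, so these are upper illustrations. For k = 5, simulation with equally correlated normal statistics gives about 18% at correlation 0.5 and about 15% at 0.7. These correlations are assumptions; the protocol gives none.

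**Primary and secondary wording.** Section 2.2.2 refers to QST differences in general and does not exclude the tolerance thresholds. If they are included, section 9 assigns them ANCOVA as primary and Mann-Whitney as secondary. If they are not, only ANCOVA applies. The text does not settle which.

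**The case against.** The strongest defence is that the direction word is a drafting slip with no numerical effect. The sentence lacks a word and follows the clinical paragraph's pattern, the endpoint that it explains is a neutral change, and the analysis is an ANCOVA with a confidence interval. This stands as far as the computation goes. A reader might infer that the trial's experimental conclusion would come out with the wrong sign; the documents do not support that, because no one-sided test or directional decision rule is written. It does not excuse the sentence, which remains the protocol's definition of benefit and is wrong by the protocol's own terms.

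A reader might also infer that ten or more thresholds are each tested at 0.05, with a false-positive risk near 40%. That goes beyond the text. The count of ten needs the wider reading of dermatomes, and nothing says that sites are tested separately or that one site suffices. Averaging or modelling the sites jointly is compatible with section 9, and such mechanics may sit in a statistical analysis plan that is not shown. What stands is that the protocol's definition does not identify the primary variable.

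Finally, section 2.2.2 might be taken as proof that the same data are both primary and secondary. It may instead mean the remaining QST measures: sensation and detection thresholds, pressure thresholds and the cold pressor test. It is ambiguous, not a demonstrated double listing.

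**Conclusion.** The point holds for the direction, with high confidence and without any outside source: section 2.2.1 contradicts sections 7.2.1 and 7.2.2, and the stated success direction of the experimental primary endpoint is reversed. The size of the error is the full sign of the definition, and nil for the magnitude of the estimate, its interval width and a two-sided p-value.

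The primary variable is also not pinned down: five thresholds on the natural reading, 10 or 11 on the wider one. The family-wise error of about 23% for five sites (about 15 to 18% at assumed correlations of 0.7 to 0.5) applies only under a rule of separate tests with any one sufficing, which the protocol does not state. The overlap with the secondary endpoints is an ambiguity to clear up, relevant because it decides between ANCOVA and Mann-Whitney.

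**What to change.** 1. In section 2.2.1, replace the reduction with *the increase in pain tolerance thresholds from pre-treatment to end of treatment, pregabalin versus placebo*. This is needed whatever is decided on the other two items.
2. State one primary test. Two workable forms are a single overall treatment effect across the five dermatomes from one repeated-measures model, or one site chosen by the sponsor before unblinding. Say whether pressure thresholds belong to it. The T10 site is a natural candidate because section 7.2.1 labels it the pancreatic site, but nothing in the protocol makes it the sole hypothesis, and the choice is the sponsor's.
3. In section 2.2.2, write *all other QST parameters*, so that the primary tolerance thresholds fall only under the ANCOVA.

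The cost is a few sentences of protocol text, with no new measurements, visits or patients. The trade-off lies in item 2. A single site makes the others supportive, while an overall effect does not localise the finding and loses sensitivity if the drug acts at one site only.
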